Whilst many decades ago newborn infants were considered passive, research has shown that the brain, not just the spinal cord, is involved in the infant’s responses, and, more importantly, the infant’s brain is active from birth [3]. Neonatal neurobehavioural examinations have been developed that assess the integrity of an infant’s central nervous system [4] and can be used as a tool to identify infants at risk of developmental disabilities [2]. These examinations include traditional neurological assessment items such as reflexes, posture and tone along with behavioural assessment items such as the infant’s ability to regulate their own level of arousal and states, to habituate, to attend and orient [5]. Neurobehavioural development of preterm infants differs from that of term born infants at term equivalent age [6,7] and has been shown to be related to environmental and biological factors [8]. Importantly, these differences in neurobehavioural developmental at term in preterm children compared with term born children are associated with later motor, cognitive and behavioural difficulties [5,9] and contribute to neurodevelopmental impairments in school-age children born preterm. A recent review of neonatal neurobehavioural assessments for preterm infants assessed the validity of the available tools for assessing neurobehaviour from birth to term equivalent age and concluded that there are several tools that are predictive of development at age one and two years’ corrected age (CA) when used at term equivalent age and beyond [2,10,11]. However, there is a lack of evidence for the discriminative, evaluative and predictive validity of these tools when administered prior to term, limiting their use in clinical practice and research with preterm infants while in the Neonatal Intensive Care Unit (NICU). It is essential that health professionals can assess neurobehaviour from birth to (i) determine whether a very preterm infant is developing normally or abnormally, (ii) assess the effects of interventions and exposure to perinatal variables, and (iii) predict whether the infant may have long term developmental problems, so that appropriate interventions can be commenced immediately. Preliminary evidence suggests that neurobehaviour in the ex-utero environment matures rapidly during the neonatal period in association with cerebral maturation in the very preterm infant. In a small study of preterm infants born between 28 and 32 weeks’ gestational age (GA), structural and biochemical cerebral maturation (from 32 to 40 weeks’ GA), as determined by Magnetic Resonance Imaging (MRI), was reported to accompany neurobehaviour maturation [12]. At term equivalent age, preterm infants had less developed grey and white matter than full term infants and less mature neurobehaviour. It is well known that the period between 20–40 weeks’ GA is one characterised by rapid and vulnerable neurodevelopment [13]. Brain structural abnormalities in neonates are readily detected with MRI, and studies have reported that infants born <30 weeks’ GA have grey and white matter abnormalities [14], white matter microstructural alterations [15], deficits in brain connectivity [16], and volume reductions in other brain regions and structures [17-19]. Despite this, there has been a paucity of information to date relating the evolution of neurobehavioral alterations prior to term with cerebral alterations, especially for the most immature infants. Brain MRI during the neonatal period in preterm infants may help us to understand how early neurobehavioural development in this period relates to brain injury or structural alterations at term-equivalent age.

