3. The validity of early neurobehavioural assessments from birth to term-equivalent age for predicting development at one and two years’ CA in very preterm children will be investigated using separate linear (continuous outcomes) and logistic (binary impairment outcomes) regression models for each neurobehavioural assessment time point according to chronological and gestational age and each outcome. Estimates of the regression coefficients and the R^2^ values (representing the proportion of variability in the outcome explained by the model) from these models will be compared with estimates from the same models using neurobehaviour at term equivalent age as the predictor to obtain an idea of the predictive ability of these early measurements compared with the measurements at term as used currently. Data from term-born controls will be used to provide a local-reference population for calculation of mild, moderate and severe developmental impairment (mild = more than 1 SD below the mean, moderate = more than 2 SD below the mean, severe = more than 3 SD below the mean on the Cognitive Composite Scale on the Bayley-III).

4. To examine symptoms of depression, anxiety, and post-traumatic stress in mothers and fathers of very preterm children at birth during the first two years of the child’s life compared with term-born controls, we will present means and 95% CI for each parental assessment at each time point. For each time point, the observation closest to the specified time for the completed week within +/− 3.5 days for weekly assessment and +/− 7 days for fortnightly assessments will be selected for each individual.

5. To examine the relationships between parental psychological wellbeing, parent and family factors, and very preterm children’s neurobehavioural development at birth, and later two year-old cognitive, motor and social-emotional developmental outcomes, we will fit separate linear regression models for each of the two year outcomes. Initially each parent and child factor will be explored using separate univariable models for each outcome before combining important factors into a single model for each outcome to assess independent predictors.

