### Sample size

A sample of 150 very preterm infants and 150 term-born controls was chosen based upon projected workload, the number of infants <30 weeks cared for each year at the Royal Women’s Hospital, and the expected consent rate for the study from families. A sample of 150 infants will enable us to estimate the mean of any neurobehavioural measure employed in this research at any time point to within +/−0.16 standard deviations (based on a 2-sided 95% confidence interval, Aim 1), and to identify correlations between observations as small as 0.2 (Aims 2 and 3), with 80% power (based on 5% significance).

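### Main aim 3 compares early with term prediction by bare coefficients and R², with no paired interval for the difference and no common set of infants, which is too imprecise to rank one against the other

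*Protocol article*

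**What the plan says.** Under Data collection & analysis, main aim 3 uses linear models for continuous outcomes and logistic models for binary impairment, fitted separately "for each neurobehavioural assessment time point according to chronological and gestational age and each outcome". Coefficient estimates and R² values "from these models will be compared with estimates from the same models using neurobehaviour at term equivalent age as the predictor". The stated purpose is "to obtain an idea of the predictive ability of these early measurements compared with the measurements at term as used currently".

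The paragraph names no interval for the difference and no rule on which infants enter each pair of models. Elsewhere in the same section and under Secondary aims, 95% confidence intervals are named for the means in main aims 1, 2 and 4 and secondary aims 1 and 2. Where trends are compared between categories or groups, an interaction term is named.

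The section on serial neurobehavioural assessments schedules examinations weekly from enrolment to 32 weeks, then fortnightly, ending at term or at discharge from the recruiting hospital. The number of early time points is not stated and differs between infants.

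Under Sample size, "A sample of 150 very preterm infants and 150 term-born controls was chosen". Main aim 3 is covered there only by the ability "to identify correlations between observations as small as 0.2 (Aims 2 and 3), with 80% power (based on 5% significance").

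**The concern.** The Background says that "there is a lack of evidence for the discriminative, evaluative and predictive validity of these tools when administered prior to term", and that this limits use of the tools in the nursery. How early prediction stands against term prediction is therefore a main product of aim 3.

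Two features make the written comparison weak. First, an R² from about 150 infants carries substantial sampling error, and so does the difference between two of them. Set side by side many times with no interval, the values invite the reader to rank time points on differences that may be noise.

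Second, the two R² values may come from different infants. Examinations start at enrolment and stop at discharge, so the infants contributing at one time are not necessarily those contributing at another. R² depends on the spread of score and outcome in the subset used. A gap between two R² values can therefore reflect who was examined rather than when.

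**Working it through.** **The article's own figures.**
- Precision of a mean: 1.96/√150 = 0.160 SD, as stated for aim 1.
- Correlation 0.2 by Fisher's z, n = ((z_α + z_β)/atanh 0.2)² + 3: one-sided n = 153 (power 79.2% at 150); two-sided n = 194 (power 69.1% at 150). The stated figure therefore reproduces as a one-sided test. That is a separate matter, noted only for completeness.
- Neither figure concerns a difference between two predictors of the same outcome. The article gives no figure for that.

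**Inputs.** From the article: 150 very preterm infants. Assumed, because not given: one score per model; correlation between early and term scores ρ = 0.3 to 0.6; 100 to 150 infants with complete data; 5 to 7 early time points; true correlations with outcome of 0.2 to 0.4.

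**Precision of one R² difference.** Let both true correlations be r = 0.3, so each R² is 0.09. For two correlations sharing an outcome:

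Var(r₁) = (1 − r²)²/n = 0.8281/n

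Cov(r₁, r₂) = [ρ(1 − 2r²) − ½r²(1 − 2r² − ρ²)]/n

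Var(R² difference) ≈ 4r² × 2[Var(r₁) − Cov(r₁, r₂)]

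At ρ = 0.5, n = 150:
- n × Cov = 0.5 × 0.82 − 0.045 × 0.57 = 0.3844
- Variance = 0.36 × 2 × (0.8281 − 0.3844)/150 = 0.00213
- SD = 0.046; half-width = 1.96 × 0.046 ≈ 0.09

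At ρ = 0.3 the half-width is 0.107 and at ρ = 0.6 it is 0.081. At n = 100 these are multiplied by √1.5 = 1.22, giving about 0.13 and 0.10. Simulation agrees: 0.081 to 0.107 at n = 150, and 0.101 to 0.133 at n = 100. The range is about 0.08 to 0.13, against an R² of 0.09.

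**Chance that a truly worse early time looks at least as good as term.** Multivariate normal simulation, 4,000 runs per cell, same infants at every time. Entries are the share of studies in which at least one early R² equals or exceeds the term R² (5 / 7 early times):

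| True r, early vs term | N | ρ = 0.3 | ρ = 0.5 | ρ = 0.6 |
|---|---|---|---|---|
| 0.2 vs 0.3 | 150 | 38% / 44% | 30% / 34% | 24% / 28% |
| 0.2 vs 0.3 | 100 | 46% / 54% | 40% / 46% | 35% / 41% |
| 0.2 vs 0.4 | 150 | 6% / 7% | 2% / 3% | 1% / 1% |
| 0.2 vs 0.4 | 100 | 13% / 16% | 6% / 8% | 4% / 5% |

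The highest cell of each block varies between runs (51% to 54%, and 15% to 16%). For one early time named beforehand, the 0.2 vs 0.3 figure is lower, about 7% to 19%. Much of the problem thus comes from scanning many times.

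**Fewer infants at the earliest times.** If early samples rise from 40 to 150 over 6 to 8 time points, the share is about 47% to 58% for a gap of 0.1 in r (0.2 vs 0.3, or 0.3 vs 0.4). It is about 13% to 23% for a gap of 0.2 (0.2 vs 0.4, or 0.3 vs 0.5).

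**The case against.** The strongest reply is that the article describes and does not decide. It asks only for an impression of relative predictive ability. It sets no threshold, does not select the best early time, and nowhere proposes replacing the term examination. It compares coefficients as well as R², and each early model also stands as a test of association in its own right. An interval for a difference is a detail that a condensed article may leave to the analysis plan, and silence is not a promise to withhold uncertainty.

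Most of this stands. A reader might go further and infer that, with no true difference, some early time would be declared as good as or better than term in about 85% of studies. The documents do not support that. With k exchangeable time points the share is k/(k + 1), which is 6/7 = 86% for six, but k is not stated, one pair gives 50%, and no rule says that any one time suffices. Nor is it an error rate: if early and term predict equally well, finding early as good as term is correct.

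The plea of missing detail does not stand. The article does state how the comparison is made: estimates against estimates. That method gives no measure of the error in the difference and allows different infants on each side.

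**Conclusion.** The point holds in a limited form. As written, the aim 3 comparison cannot distinguish a real early match with term from sampling error or from a change in the infants examined. The half-width of one R² difference (about 0.08 to 0.13) is similar to the whole R² of a 0.3 correlation. A modest true advantage for term is hidden at one early time or more in about 24% to just over 50% of studies; a larger advantage is hidden in only about 1% to 15%.

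These figures rest on the assumed correlations, number of time points and complete-data sample, with everyone seen at every time. Fewer infants at early times makes them worse. They describe how informative the displayed values are. They are not the error rate of a decision rule, since the article has none. The planned models are sound, and only the way in which they are compared needs to change.

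**What to change.** For each early time point, report the early-minus-term difference in R² for continuous outcomes, and in AUC for binary outcomes, with a 95% bootstrap interval. Resample infants and refit both models in each resample. Fit both to the infants who have the early assessment, the term assessment and the outcome, and give that number. Show all time points together, not the best one alone.

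The cost is a short bootstrap on models already planned, with no new data. The downside is wide intervals and a smaller common sample at the earliest times, so fewer firm statements about early against term prediction will be possible.

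A stated acceptable loss, a single age scale or an optimism correction could be added, but these are preferences and the point does not depend on them.

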### Aims

The main aims of this study are to:

1. Describe the evolution of early neurobehavioural development in infants <30 weeks from birth to two years’ CA compared with children born at term, and to explore how neurobehaviour is influenced by perinatal variables.

2. Explore the relationship between early neurobehavioural development and neonatal brain abnormalities (development and injury) at term using multi-modal MRI in infants <30 weeks at birth.

3. Investigate the predictive validity of neurobehavioural assessments during the early neonatal period for developmental outcomes at one and two years’ CA in infants <30 weeks at birth.

4. Examine symptoms of depression, anxiety, and post-traumatic stress in mothers and fathers of infants <30 weeks at birth and to describe changes in parental psychological wellbeing over the first two years of the child’s life compared with children born at term.

5. Examine parental psychological wellbeing, and parent and family factors during the neonatal period as predictors of development at one and two years’ CA in children born <30 weeks, and whether these relationships are similar in children born at term.

In addition, secondary aims of this study are to:

1. Explore whether neurobehavioural examinations in the preterm period relate to concurrent physiological status (i.e. heart rate and oxygen saturations) in infants <30 weeks at birth.

2. Describe the parenting beliefs and practices of parents of infants <30 weeks at birth across the first two years of the child’s life.

3. Examine whether parental psychological wellbeing from birth to one year CA is associated with the parent–child relationship and child development when the child is one and two years’ CA in infants <30 weeks at birth.

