PCL-S	The *Posttraumatic Stress Disorder Checklist Specific Version*[69] (PCL-S) will be used to assess symptoms of posttraumatic stress disorder (PTSD). The PCL-S consists of 17 items (total score range 17 to 85). The questions are asked in relation to a nominated specific traumatic event, in this case, the birth of their very preterm infant. There is evidence for good test-retest reliability, internal consistency and convergent validity [70]. Only parents of preterm infants will complete the PCL-S.
IPIP-NEO	Neuroticism, or negative affectivity, will be measured with the 10-item Neuroticism scale of the *International Personality Item Pool Five Factor Personality Inventory* (IPIP-NEO) [71]. The Neuroticism scale selected for the present study is from a 50-item self-report version of the NEO PI-R, named the IPIP-NEO [72]. Responses on the Neuroticism scale are scored on a 5-point scale.
PSOC	The *Parenting Sense of Competence Scale* (PSOC) assesses parental satisfaction and efficacy in the parenting role, with higher scores representing higher satisfaction and efficacy in parenting. It is a 16 self-report measure with each item rated by parents on a 6-point rating scale. The PSOC has been widely used and there is good evidence for the validity of the measure [73].
CISS	The *Coping Inventory of Stressful Situations* (CISS) is a 48-item inventory which will be used to measure three major types of coping styles in an individual, including Task-Oriented (problem-solving), Emotion-Oriented (focuses on consequent emotions, becoming angry/upset), and Avoidance Coping (distraction and social diversion) [74]. Parents will be asked to rate each item on a 5-point scale ranging from (1) “not at all” to (5) “very much”.
PSI-LSS	The *Life Stress Scale* from the *Parenting Stress Index (PSI-LSS)*[75] assesses how many of 19 significant life events have occurred for parents within the last 12 months such as divorce, went deeply into debt, entered new school.
Demographic & family questionnaire	Items include relationship to child, whether the parent is the primary caregiver, number of other children in the home, cultural background.
Parent mental health history questionnaire	Five items will assess parental cigarette, alcohol and recreational drug use, and mental health service access history.

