CSBS-DP	The *Infant-Toddler checklist* from the *Communication and Symbolic Behavior Scales Developmental Profile* (CSBS-DP) [81] is a 24 item screening tool designed to measure 7 predictors of language including emotion and eye gaze, communication, gestures, sounds, words, understanding and object use in children aged between 6 and 24 months of age.
Social Risk Index	A *Social Risk Index* (family demographic questionnaire) [37] score will be calculated based on a combination of family structure, education of primary caregiver, employment of primary income earner, language spoken at home and maternal age at the birth of the child. Higher scores indicate higher social risk.

Table 5 provides an overview of the questionnaire measures to be collected at each time point. For term-born infants, birth and term are the same time point in Table 5.

**Table 5 T5:** Administration timetable for parent completed questionnaires

	**Birth**	**F/night***	**Term**	**3mth (CA)**	**6mth (CA)**	**12mth (CA)**	**18mth (CA)**	**24mth (CA)**
CES-D	√	√	√√	√√	√√	√√	√√	√√
HADS	√	√	√√	√√	√√	√√	√√	√√
PCL-S			√			√		√
IPIP-NEO	√							
PSOC					√√	√√		√√
PSI-LSS	√√					√√		√√
CISS	√√				√√			
Demographic & family questionnaire	√√							
Parent mental health history questionnaire			√√			√√		√√
Parenting practices					√√	√√		√√
ITSEA						√√		√√
MacArthur CDI								√√
FAD								√√
ITSP								√√
CSBS-DP								√√
Social Risk Index	√√					√√		√√

Note. *F/night = administered fortnightly from first neurobehavioural assessment until term equivalent age; √√ = both preterm and term-controls; √ = preterm only; CES-D = Centre for Epidemiological Studies Depression Scale; HADS = Hospital Anxiety and Depression Scale; IPIP-NEO = International Personality Item Pool Five Factor Personality Inventory-NEO, PCL-S = Posttraumatic Stress Disorder Checklist Specific Version; CISS = Coping Inventory for Stressful Situations; PSOC = Parenting Sense of Competence Scale; PSI-LSS = Parenting Stress Index – Life Stress Scale; ITSEA = Infant-Toddler Social and Emotional Assessment, MacArthur CDI = MacArthur Communicative Development Inventories, FAD = Family Assessment Device, ITSP = Infant Toddler Sensory Profile, CSBS – DP = Communication and Symbolic Behavior Scales Developmental Profiles.

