### Secondary aims

1. To explore whether the neurobehavioural trajectory varies according to concurrent physiological status, physiological status variables of interest will be dichotomised or separated into distinct categories (e.g. stable versus unstable). The mean (and 95% CI) scores at each time point (as described above) will be plotted separately for children within each category. Trends over time will be modelled using separate mixed effects regression models for each of the neurobehavioural scores including a fixed effect for time (gestational and chronological age) and physiological status and an interaction between time and physiological status to assess whether the effect of time is different in the different categories of this variable.

2. To describe the parenting beliefs and behaviour of parents of very preterm children across the first two years of the child’s life compared with term-born controls, we will present means and 95% CI for each parental assessment at each time point from term equivalent age to two years. Trends over time will be compared between the two groups using separate mixed effects regression models for each parent, with a fixed effect of time (gestational and chronological age) and group as well as an interaction between time and group. Models will also include a random effect to allow for repeated measures within a parent.

3. To examine whether parental psychological wellbeing is associated with the parent–child relationship when the child is one and two years’ CA, average scores for parental mental health from birth to 6 months, and from one to two years will be used as predictors of the 6 outcomes scales of the parent–child relationship measure at one and two years CA respectively. Separate linear regression models will be used for mothers and fathers to examine these relationships.

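### Aim 4 promises a post-traumatic stress comparison for which controls give no data, and compares CES-D and HADS at corrected-age points where preterm parents are further from the birth

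*Protocol article*

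**What the plan says.** In the protocol article, Aims, main aim 4 is to examine parental symptoms and "to describe changes in parental psychological wellbeing over the first two years of the child", compared with the term group. Under Data collection & analysis, aim 4 covers three constructs, "To examine symptoms of depression, anxiety, and post-traumatic stress in mothers and fathers of very preterm children at birth", and then states, for the comparison with term controls: "we will present means and 95% CI for each parental assessment at each time point". It adds selection windows of 3.5 days either side for weekly points and 7 days either side for fortnightly points. It names no model and no time scale.

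On who completes what, Table 4 says: "Only parents of preterm infants will complete the PCL-S". The event asked about is "in this case, the birth of their very preterm infant". Table 5 agrees: the PCL-S is marked preterm only at term, 12 and 24 months. The Abstract, however, says that parents in both groups complete questionnaires on all three constructs.

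On timing, Table 5 marks CES-D and HADS as preterm only at *Birth* and fortnightly, and as both groups from *Term* to 24 months. The points after term are headed corrected age. The text above the table adds: "For term-born infants, birth and term are the same time point in Table 5".

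Secondary aim 2, on parenting beliefs and behaviour, gives the same means and intervals and then a mixed model for each parent, "with a fixed effect of time (gestational and chronological age) and group as well as an interaction between time and group", with a random effect for repeated measures within a parent.

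**The concern.** The post-traumatic stress part of the comparison has data in one arm only. An unseen analysis plan could not repair this, because the control data are not collected.

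For depression and anxiety, the first column that both groups share sets control parents close to delivery beside preterm parents many weeks after it. Later columns carry the same offset. The Background treats time since birth as substantive: it wants to know how parents cope in the first weeks and how wellbeing changes. If distress falls with time since birth, a comparison at *Term* could hide an excess in preterm parents, because their acute phase has partly passed. If distress builds over a long hospital stay, it could produce a difference of another kind. Either way, a gap between two means in one column mixes the effect of group with the effect of elapsed time.

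The aim also speaks of change compared with controls, and a list of means with intervals stops short of estimating that.

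**Working it through.** **Post-traumatic stress.** Four places bear on this: the Abstract (both groups), the Table 4 entry (preterm parents only, asked about the preterm birth), Table 5 (preterm only at all three points) and the Aim 4 analysis (compared with controls). Table 4 and Table 5 agree with each other and conflict with the other two. Table 4 lists no other post-traumatic stress instrument, so the number of control observations is zero.

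**Time since birth.** The article states no figure for this gap, so there is none to reproduce. Inputs:
- Preterm infants: born before 30 weeks (inclusion criteria), so 29 weeks 6 days (29.86 weeks) at most.
- Youngest preterm infant: no minimum is stated. I assume 23 weeks, a figure that appears in the article only as the lower age limit of the Premie-Neuro.
- Controls: more than 36 completed weeks, taken as 37 weeks or later, with no upper limit.

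Against a control born at 40 weeks, or a control followed by chronological age, the gap is 40 − preterm gestation:
- 40 − 29.86 = 10.14 weeks
- 40 − 23 = 17 weeks (16 if the youngest is 24 weeks, 18 if 22 weeks)

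If corrected age is applied to controls too, the gap is control gestation − preterm gestation:
- smallest: 37 − 29.86 = 7.14 weeks
- largest: 42 − 23 = 19 weeks, with both ends assumed

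Weeks since birth at the same corrected age, control born at 40 weeks:

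| Point | Control | Preterm, 29w6d to 23w | Ratio |
|---|---|---|---|
| Term | 0 | 10.1 to 17 | – |
| 3 months | 13 | 23.1 to 30 | 1.8 to 2.3 |
| 6 months | 26 | 36.1 to 43 | 1.4 to 1.7 |
| 12 months | 52.2 | 62.3 to 69.2 | 1.2 to 1.3 |
| 24 months | 104.4 | 114.5 to 121.4 | 1.1 to 1.2 |

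The offset in weeks is constant, but relative to elapsed time it shrinks from about double at 3 months to 10–16% at 24 months. For scale, Aim 4 selects observations to within half a week or a week, while the smallest offset between groups at the same corrected age is about 7 weeks.

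**Change.** For two time points with standard deviations s1 and s2 and within-parent correlation r, the variance of the mean change in n parents is (s1² + s2² − 2·r·s1·s2)/n. Separate means and intervals do not carry r, so they give no standard error for change within a group or for the difference in change between groups. If some questionnaires are not returned, means at different points also come from different sets of parents. The group-by-time term in the secondary aim 2 model estimates the missing quantity directly.

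**The case against.** The best reply is that Aim 4 is descriptive. It says examine and describe, and group means with intervals are a legitimate description. The article is condensed, and a model may stand in the full protocol or analysis plan. This is fair: the missing model cannot be called an error, and a reader should not infer that none is planned. What remains is that a main aim about change versus controls has a thinner stated comparison than a secondary aim in the same article.

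On timing, Aim 4 does not say that groups will be compared column by column. Because birth and term are one point for controls, their first score can be set against either the preterm *Birth* or the preterm *Term* score, and both are collected. Corrected age also aligns families by the child's developmental stage and matches the child outcomes. These points stand. They make the choice of time axis a choice of question, so it would go too far to say that time since birth is the only right axis. But the article should state which question is being answered. Aims 1 to 3 and secondary aims 1 and 2 name both gestational and chronological age; Aim 4 names neither.

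The term assessment window of 38 to 44 weeks also blurs the gap for individual pairs. At the extreme, a preterm infant born at 29w6d and seen at 38 weeks is 38 − 29.86 = 8.1 weeks from birth, and a control born at 37 weeks and seen at 44 weeks is 7 weeks from birth. The direction still holds, but the size for a given pair can be small.

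A reader might also infer that the groups will be judged by whether their intervals overlap, and object to the resulting error rate. The article does not support that: it says only that means and intervals will be presented, and gives no decision rule or test for Aim 4.

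**Conclusion.** The concern holds, at the level of something that should be fixed.

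The post-traumatic stress contradiction is firm and needs no assumption. In practice it is a wording fault, since nobody could run the comparison.

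The time-since-birth offset is firm in direction. At the same corrected age it exceeds 10 weeks against a control born at 40 weeks, and is at least about 7 weeks against the earliest eligible control. The upper figure of about 17 weeks is not in the article; it rests on an assumed minimum of 23 weeks and a 40-week reference. It would be tempting to call every shared column equally compromised, but the article does not support that: the relative offset is small by 24 months, and no bias in CES-D or HADS points can be estimated from the document. The points at risk are *Term* and 3 months.

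The lack of an estimate of difference in change is a mismatch between main aim 4 and its stated analysis, made visible by secondary aim 2.

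**What to change.** 1. Restrict the PCL-S to a description in preterm parents, and reconcile the Abstract, Table 4, Table 5 and the Aim 4 analysis text accordingly.
2. For CES-D and HADS, extend the secondary aim 2 model to Aim 4: group, continuous time, group-by-time interaction and a random effect per parent, fitted separately for mothers and fathers.
3. Report that model on both time since birth and corrected age, and say which question each answers. Keep the means and intervals as the descriptive display.
4. Show the controls' first score beside the preterm *Birth* score as well as the preterm *Term* score.

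The cost is a few sentences and a few extra models on data already scheduled for collection. The one real drawback is that questionnaire dates do not line up across groups on time since birth. Time must therefore be modelled as continuous, and some comparisons rest on interpolation between visits.
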